### Patients, eligibility and generalisability

All patients are eligible to enter the study if they are diagnosed with rheumatoid arthritis (either 2010 ACR RA and/or 1987 RA criteria and/or clinical diagnosis of the treating rheumatologist, fulfilled at any time point between start of the disease and inclusion), and of any disease duration, use etanercept or adalimumab in any stable dose for at least 6 months, and are in low disease activity state [26,27]. Previous dose reduction of the TNF blocker is allowed when more than 6 months ago. All background medication including DMARDs (either monotherapy or in combination) and prednisone equivalent up to 5 mg are allowed during the study and have to be stable for at least four weeks before inclusion. Consenting patients are randomly allocated in a ratio of 2:1 to the intervention or the control group, stratified for TNF blocker (adalimumab and etanercept).

We have chosen to operationalise low disease activity state by either a DAS28CRP < 3.2 or judgment of low disease activity by the rheumatologist at two subsequent visits at least 3 month apart. This means also patients with a DAS28 ≥ 3.2, but judged to have a low disease activity by their treating rheumatologist, are eligible for inclusion. This is firstly because several biologic registries show that mean DAS28 in TNF Blocker treated patients in clinical practice is around 3.2 [28]. This means that over 50% of the patients has a DAS28 ≥ 3.2, and even more are not in remission, but that both the patient and rheumatologist judge the disease activity to be low enough not to warrant switch of treatment. Limiting inclusion to only patients with DAS28 < 3.2 or even < 2.6 would therefore limit generalisability to current treatment practices. It might be rebutted that these higher disease activity scores reflect undertreatment and thus result in suboptimalisation. A DAS28 can however be inflated by OA associated joint pain, concomitant fibromyalgia or spuriously elevated ESR. This is also the rationale for use of DAS28CRP instead of DAS28 ESR. Another important consideration is that we treat RA patients for two reasons: firstly to improve current signs and symptoms, and secondly to prevent joint damage. With respect to the first reason, it is important to note that the patient acceptable symptom state of the DAS28, has been found to be around 3.5 to 3.9, clearly higher than the currently advocated treatment aims of 2.6 or 3.2 [29]. For prevention of joint damage it is important to realize that not all patients have high risk of erosive disease and a need for prognosis modification [30]. Therefore, accepting somewhat higher disease activity can be legitimate and is indeed part of clinical practice. Of note, per October 19, 2012, all patients (n = 180) have been enrolled and randomised. Mean DAS28CRP is 2.2, and 8% of patients had a DAS28 > 3.2.

Because we aimed for maximal generalisability, we chose to only exclude patients if they have co morbidity which also requires treatment with anti-TNF and thus prevents dose reduction (e.g. Crohns disease), or when it is to be expected that the outcome cannot be measured (short life expectancy, planned major surgery).

### Interventions

#### **
*Control*
**

Patients in the usual care group will continue treatment by their own rheumatologist, following a standardized protocol based on the tight control/treat-to-target principle and aiming to maintain low disease activity. Visits are planned every 3 months and patients are encouraged to contact the outpatient clinic if they experience more complaints in between visits. CRP based DAS28 measurements are provided on the day of the outpatient visit to the treating rheumatologists. The standardized protocol offers protocollised treatment suggestions when there is a flare, including a treatment algorithm and dosing of the drugs. The research physician monitors protocol adherence of the rheumatologists and will - where needed - give feedback and advice to the rheumatologist. Treatment choices, however, are left to the discretion of the treating rheumatologist. This way it is ensured that positive study results can be achieved also in clinical practice. Treatment will be changed in case of a confirmed flare (the definition of flare will be discussed separately). A one time flare will be, if necessary, bridged with glucocorticoids. Also, dose reduction or stopping, for any reason, was allowed in the control arm, as this is sometimes-although infrequent-also part of usual care (5). In summary, the control condition exist of tight control by patients own rheumatologist, and all treatment choices are allowed.

Of note, although called usual care, tight control care has thus far not consistently been implemented in clinical care in the Netherlands [31]. However, opting for a standard care arm without tight control would result in underestimation of possible drawbacks of dose reduction, as these effects would be ameliorated by the difference in tight control.

#### **
*Intervention*
**

The intervention group receives identical care as the control group, with addition of a dose reduction and withdrawal strategy protocol and feedback and advice to treating rheumatologist. This strategy is directly adapted from the Dutch Society of Rheumatology biological guideline [32]. If a patient uses adalimumab, the interval will be stepwise increased every three months from 14 to 21 to 28 days, after that the adalimumab will be stopped. For etanercept, the interval will be increased from 7 to 10 to 14 days and stopped thereafter. If a patient uses a different dose regimen at start, an alternative dose reduction strategy is used. Patients already on a longer dosing interval will step in at the nearest dosing interval. Patients on a shorter dosing interval will also stepwise increase the interval to stop after 6 months using an accelerated strategy. The three month interval is based on data that shows that most of the flaring after dose reduction occurs within 3 months [14].

The dose reduction steps from 100% to 66% and 50% and thereafter stop are based on the notion that relatively small dose reduction seems to be feasible in a large proportion of patients, and therefore will lead to sizable reduction in total volume and costs of the TNF blocker [14,20]. Indeed, although stopping the TNF blocker obviously saves more drug per patient than dose reduction, the total volume of saved drugs is the same in patients that stop or are only dose reduced, because the latter group is much larger [14]. Also, although we cannot substantiate this, dose reduction until stop feels more appropriate for patients than just stopping the drug.

When a confirmed flare occurs, the interval is decreased back to the last effective interval. When there is still no improvement of disease activity eventually after reintroduction of the original interval and dose, the patient will be advised to switch to the next biologic or DMARD according to the treatment protocol.

### Outcome measures

The outcome measures used in this study include disease activity (DAS28CRP based RA Flare criterion, mean and time integrated DAS28CRP), function (HAQ DI), radiological damage (Modified Sharp van der Heijde score, MSvdH), Adverse events (CTC 4.0 criteria), utility (Euroqol 5D 5 L) and costs [33-39].

#### **
*Definition of flare*
**

RA Flare in this study is defined in both treatment arms as a DAS28 increase compared to baseline of more than 1.2 or a DAS28 increase of more than 0.6 with a current DAS28 ≥ 3.2 at two separate timepoints at least 4 weeks apart. This criterion has been validated recently, and has been shown to have the optimal tradeoff between sensitivity and specificity, and the best construct and criterion validity [40]. As it has been shown that flares are frequently temporary and occur and disappear without regimen change, a flare is only considered a flare if it is confirmed after at least 4 weeks [11]. Patients are however not left untreated, and when a flare in disease activity occurs, all bridging therapy including i.a. or im steroids or NSAID can be given and are allowed. Of note, flares are defined with change compared to baseline, not compared to the last visit, to prevent undertreatment in patients with a slight increase in disease in subsequent visits.

When the flare is confirmed after 4 weeks, in both treatment arms patients receive optimal treatment for the flare, for example protocollised reinstallment or dose increase of the TNF blocker or change to another biologic or DMARD. Only patients in whom the flare persist longer than three months (in spite of all treatment intensivation) are classified as having persistent flare, the primary outcome of this study.

#### **
*Secondary outcomes*
**

##### 

**Cost effectiveness** A separate calculation will be made for the 9 months induction phase and the 12 months maintenance phase for the reasons described above. The cost analysis includes both direct and indirect costs, from a society perspective, and consist of two main components: determination of volumes of care and determination of cost prices for each volume of consumption. Volumes of care (registered out-patient clinic visits, medication use, and work-related absenteeism) are multiplied with the cost prices to calculate costs. Cost prices for medication are retrieved from the Dutch National tariff list provided by the Dutch Board of Health Insurances. The standard cost prices from the ‘Dutch Guideline for Cost Analyses’ are used for valuation of hospital related care and work-related absenteeism.

##### 

**Radiographic damage** Change in radiographs of hands and feet between baseline and study end are compared between intervention and usual care by calculating the change in MSvdH score, scored chronologically in random order [35]. The smallest detectable difference (SDD) within this 18 months timeframe in this group of patients with established RA is expected to be 8 points, comparable with the widely validated minimal clinical important change (MCIC) of 5 point per year [38,39,41]. Proportions of patients showing radiographic joint damage progression exceeding the MCIC are then calculated.

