## Methods/Design

This pragmatic, open, randomised, controlled, stratified non-inferiority strategy trial with cost effectiveness analysis is currently being performed (inclusion finished October 2012) at the departments of rheumatology of the Sint Maartenskliniek in the cities of Nijmegen and Woerden, the Netherlands. The study has received ethical review board approval (number NL37704.091.11) and has been registered (Dutch Trial Register NTR3216). A data safety monitoring board (DSMB) is installed. Every three months data on recruitment, efficacy, safety, protocol adherence and protocol updates and all aspects concerning GCP are reviewed with three independent DSMB members, an internal medicin physician, a pharmacist and an epidemiologist.

We made a distinction in an induction phase (months 0-9 after the first dose reduction) and a maintenance phase (months 6-18), because the cost effectiveness is very different between these two time periods [14] (Figure 1). In the induction phase, medication costs are still high, patients are sometimes seen more often, and quality of life might be compromised by temporary flares. Therefore, the cost effectiveness ratio found in the stable maintenance phase can be better interpreted for subsequent years.

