### Objectives

The aim of the study is to test whether a tight control strategy with protocollised dose reduction and discontinuation in RA patients using TNF blockers is non-inferior with regard to disease control compared to a strategy without dose reduction attempt, and superior with regard to cost effectiveness. This translates in the following research questions:

#### **
*Primary objective*
**

– To assess whether the difference in cumulative incidence in persistent RA flares with a duration > 3 months between the intervention group and the usual care group of RA patients does not exceed the non-inferiority margin of 20% after 18 months of follow up.

#### **
*Secondary objectives*
**

– To compare the cumulative incidence of patients fulfilling flare criteria in the intervention and the usual care group after 9 months and after 18 months of follow up.

– lTo compare the cumulative incidence of patients with persistent RA flare resulting in change of biological between the intervention and the usual care group after 9 months and after 18 months of follow up.

– To compare the proportion of patients with a DAS28 < 3.2, DAS28 < 2.6 and fulfilling remission criteria according to ACR/EULAR criteria between the intervention and usual care group at 9 and 18 months follow up.

– To compare the mean DAS28 and the mean time averaged DAS28 between the intervention and usual care group at 9 and 18 months follow up.

– To compare the proportion of patients using NSAIDs, glucocorticoids or DMARDs between the intervention and usual care group at 9 and 18 months follow up.

– To compare the mean Health assessment questionnaire disability index (HAQ-DI) between intervention and usual care group at 9 and 18 months follow-up.

– To compare the proportion of patients with a change in modified Sharp-van der Heijde Score exceeding the minimal clinical important change (MCIC) between the intervention and usual care group at 18 months.

– To compare the proportion of patients developing adverse events with special attention for allergic/injection reactions between the intervention and usual care group.

– To estimate the decremental cost effectiveness ratio of a protocollised dose reduction/withdrawal strategy of adalimumab or etanercept compared to usual care for the 9 months induction phase and for the 12 months maintenance phase.

#### **
*Study design rationale*
**

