An interesting alternative for a primary outcome of non-inferior disease control would be to prove superior cost effectiveness of the alternative strategy. This would require proving that either the alternative strategy does not lead to loss of Quality Adjusted LifeYears (QALY) but saves costs (dominant strategy), or that the ratio of saved costs and loss of QALY is favourable. Of note, instead of the common term incremental cost effectiveness ratio (ICER), this approach results in a decremental cost effectiveness ratio (DCER), that states the amount of costs saved per lost QALY. The use of this kind of analyses as primary research question is however challenging due to several issues, and therefore very infrequently employed [25]. Firstly, due to the bootstrapping methods that are used to calculate the DCER, a formal sample size calculation is not possible. Secondly, quality of life is only moderately correlated with RA disease activity, posing a real chance of false reinsurance when quality of life does not seem to be compromised. Thirdly, although ICERs of under 40.000 euro per gained QALY are widely accepted as cost-effective , no such clear-cut threshold is available for DCERs. Although the symmetry of using also 40.000 as threshold for DCER seems attractive, as these saved cost can be used elsewhere in health care system to get more quality of life improvement than was lost, it seems awkward to provide suboptimal therapy in relatively low cost effectiveness ranges. However, it can be argued that when the situation was reversed, e.g., when usual care would be to attempt dose reduction, the alternative of continuing medication would not be considered cost-effective when data shows an ICER clearly over 40.000. Interpretation of DCER seems therefore coloured by anchoring to either the existing and/or the alternative strategy. Anyway, a high DCER of for example > 100.000 saved per lost QALY would probably meet wide acceptance from a cost effectiveness point of view [25].

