### Planned data analysis

All statistical analyses are performed using STATA/IC 10.1 for Windows. Analyses will be done on intention to treat (ITT) basis and also per protocol basis, the latter because ITT analyses might underestimate differences between treatment arms in non-inferiority studies, resulting in a false positive study [25]. Number and reasons for exclusion and dropout are reported to ensure internal validity. Missing data on determinants/covariates will be described using descriptive analyses and missing data mechanisms will be studied. Missing values will be imputed using multiple imputation when meeting the assumption of missing (completely) at random, as imputation will increase precision and possibly reduce bias. Logistic regression models with the indicator variable as outcome and the other variables as covariates will be used to check these assumptions. Multiple imputation using chained equations will then be used to estimate missing values. Descriptive statistics will be provided using mean +/-SD, median (p25-p75) or frequencies/percentages depending on the type distribution of the data.

The primary outcome, cumulative incidence of persistent flare is calculated in both groups. The two proportions are then compared using Fisher exact testing. The cost and quality of life are compared between intervention and usual care group for the induction phase and for the maintenance phase separately. Direct costs and indirect cost will be calculated, as will utility based on EUROQOL-5D-5 L. Thereafter, when the intervention is not a clearly dominated or dominant strategy, a decremental cost effectiveness ratio will be estimated using bootstrapping, expressed as saved costs divided by loss in quality of life.

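### Cost effectiveness is planned only for two overlapping windows (months 0–9 and 6–18), so the strategy-level aim has no single estimate over the 18 randomised months

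*Protocol article*

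**What the plan says.** Under Objectives, the overall aim has two parts: non-inferior disease control, and a strategy that is "superior with regard to cost effectiveness". The economic secondary objective in the same section asks for a DCER for the 9-month induction phase and for the 12-month maintenance phase.

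The cost-effectiveness paragraph under Outcome measures repeats this: "A separate calculation will be made for the 9 months induction phase and the 12 months maintenance phase". Planned data analysis says that costs and quality of life are compared "for the induction phase and for the maintenance phase separately", and that a DCER follows by bootstrapping unless the intervention is clearly dominated or dominant.

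Methods/Design fixes the windows: "We made a distinction in an induction phase (months 0-9 after the first dose reduction) and a maintenance phase (months 6-18". It explains that in induction "medication costs are still high, patients are sometimes seen more often, and quality of life might be compromised by temporary flares", and concludes that "the cost effectiveness ratio found in the stable maintenance phase can be better interpreted for subsequent years".

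The Abstract mentions a DCER between groups without naming a period. No section names a cost, QALY or DCER comparison from baseline to month 18.

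**The concern.** Patients were randomised to strategies followed for 18 months, and a patient reaches the maintenance state only by passing through induction. A claim about the strategy therefore has to put everything it costs and everything it loses on one account. The plan keeps two accounts, and neither covers the whole period.

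The protocol expects the phases to differ in a particular direction: less saving and possibly poorer quality of life early, and a steadier, more favourable picture later. If that happens, the maintenance ratio will flatter the strategy and the induction ratio will understate it. No planned figure would say where the whole lies.

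The dominance rule adds a second route to an over-favourable reading. If it is applied by phase, maintenance could be called dominant even though the strategy cost QALYs in months 0–6.

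**Working it through.** **Windows.** Induction is 9 − 0 = 9 months and maintenance is 18 − 6 = 12 months, which reproduces the stated lengths. Their sum is 21 months against 18 of follow-up, so 21 − 18 = 3 months (6–9) are counted twice.

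**Which losses meet which savings.**
- Losses in months 0–6 meet savings in months 0–9 only.
- Losses in months 6–9 meet savings in both windows.
- Losses in months 9–18 meet savings in months 6–18 only.

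The gap is therefore specific: losses in months 0–6 are never set against savings after month 9.

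**General form.** Let S1 and Q1 be the savings and QALY loss in months 0–6, and S2 and Q2 those in months 6–18. Then

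maintenance DCER / 18-month DCER = [S2 / (S1 + S2)] × (1 + Q1/Q2).

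Drug price cancels. Maintenance looks better than the whole whenever Q1/Q2 exceeds S1/S2.

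**Illustration.** The documents give no cost or utility figures, so these inputs are assumptions except where noted. Only drug savings are counted.
- Share of full-dose drug saved: 34% in months 0–3 and 50% in months 3–6, from the 66% and 50% steps under Interventions, assuming that every patient follows both steps.
- Share saved in months 6–18: s = 0.40 to 0.60 (assumed). The lower end is close to what follows from the expectation under Sample size of about 60% reduced and 15% stopped: 0.60 × 0.40 + 0.15 = 0.39, with 0.40 taken between the two steps.
- Mean utility loss: u = 0.01 to 0.05 in months 0–9 and v = 0 to 0.005 after month 9 (assumed).

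Savings in months of full-dose drug are 3 × 0.34 + 3 × 0.50 = 2.52 (months 0–6), 3s (months 6–9) and 9s (months 9–18). QALY losses are 6u/12, 3u/12 and 9v/12.

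Worked case, s = 0.40, u = 0.03, v = 0.005:
- Induction: (2.52 + 1.20) / (0.015 + 0.0075) = 165
- Maintenance: (1.20 + 3.60) / (0.0075 + 0.00375) = 427
- 18 months: 7.32 / 0.02625 = 279
- Maintenance / 18 months = 1.53

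| s | u | v | Induction | Maintenance | 18 months | Maintenance / 18 months |
|---|---|---|---|---|---|---|
| 0.40 | 0.01 | 0.005 | 496 | 768 | 651 | 1.18 |
| 0.40 | 0.05 | 0 | 99 | 384 | 195 | 1.97 |
| 0.60 | 0.01 | 0.005 | 576 | 1152 | 864 | 1.33 |
| 0.60 | 0.05 | 0 | 115 | 576 | 259 | 2.22 |

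(Ratios are months of full-dose drug saved per QALY lost.)

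Over the grid, the maintenance ratio is 1.2 to 2.2 times the 18-month ratio and the induction ratio is 0.44 to 0.76 times it. Months 0–6 hold 44% to 67% of the total QALY loss.

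**Adding the two windows does not repair this.** At s = 0.40 the sum gives 8.52 months of drug saved against a true 7.32 (16% too much). At s = 0.60 it gives 11.52 against 9.72 (19% too much). QALY loss is overstated by 22% to 33%.

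**How the timing of the loss matters.** Assume a drug cost of 14,000 euro a year. Savings are 14,000 × 0.25 × (1/3 + 1/2) = 2,917 in months 0–6 and 14,000 × 0.39 = 5,460 in months 6–18, 8,377 in all.
- Loss of 0.06 spread evenly over months 0–9, then 0.005 a year: maintenance 5,460 / 0.02375 ≈ 230,000; 18 months 8,377 / 0.06375 ≈ 131,000; factor 1.75.
- Loss of 0.06 wholly in months 0–6 and only 0.005 over months 6–18: maintenance 5,460 / 0.005 ≈ 1,090,000; 18 months 8,377 / 0.065 ≈ 129,000; factor about 8.5.

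The second case needs almost the whole loss to fall before month 6.

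**The case against.** The split is prespecified and reasoned. Methods/Design gives the maintenance ratio a limited use, projection to later years, and no section bases a conclusion on maintenance alone. Induction is reported beside it, so its loss is not hidden. The overall aim is translated into a per-phase objective, and the plan answers that objective. The article is condensed, the assessment schedule sits in an additional file that is not shown, and an 18-month analysis could exist in the full plan.

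Much of this stands, and it rules out two stronger readings. A reader might infer that induction losses are never weighed against later savings. That is not so: losses in months 6–9 are inside the maintenance window, and all induction losses are weighed against induction savings. A reader might also infer that the cost-effectiveness question is left unanswered. That is not so either: the per-phase question is answered, and what is missing is an estimate for the strategy as a whole.

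What does not stand is the appeal to condensation. Three sections state the per-phase choice outright, so this is not a detail left to a fuller document. The reason given for the split supports reporting the maintenance ratio as a projection, but it does not justify leaving out the randomised period as a whole.

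**Conclusion.** The point holds in limited form. The plan has no cost, QALY or DCER result for months 0–18, its two windows overlap by three months and cannot be summed, and the strategy-level economic aim therefore has no single estimate. A maintenance-only ratio, or dominance in maintenance alone, can look better than the whole strategy.

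The direction rests on the protocol's own expectation that quality of life may suffer in induction. With the assumed savings, maintenance looks better once the monthly loss in months 0–6 exceeds about 1.05 times (s = 0.40: 2 × 2.52/4.80) or 0.70 times (s = 0.60: 2 × 2.52/7.20) that in months 6–18. The size is uncertain: roughly 1.2 to 2.2-fold on the assumed inputs.

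A reader might infer a gap of 8-fold or more, or phase ratios on either side of the 40.000 reference value. The documents support neither. The first needs nearly all the loss before month 6. The second appears only if induction is cut to months 0–6. Over the protocol's nine months, savings are 2,917 + 1,365 = 4,282 euro. Early losses of 0.06 and 0.08 then give about 4,282 / 0.06125 ≈ 70,000 and 4,282 / 0.08125 ≈ 53,000. What can still occur is phase ratios on either side of the higher value in the outcome rationale, where "a high DCER of for example > 100.000 saved per lost QALY would probably meet wide acceptance".

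This is a secondary outcome. The primary non-inferiority conclusion is unaffected.

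**What to change.** Add a randomised ITT comparison of total costs and total QALYs from baseline to month 18, counting months 6–9 once, and name it as the main economic result. Apply the dominance check and the bootstrapped DCER to that comparison, and base the conclusion on cost effectiveness on it. Keep the induction and maintenance results as supporting, and present the maintenance ratio as a projection for later years, shown beside the induction loss.

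The cost is one more bootstrap run and a few lines of plan wording. The three-monthly visits to month 18 should supply the data, although the article does not show the economic assessment schedule. The headline figure may be less favourable than the maintenance ratio alone.
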